#### Psychosocial functioning, quality of life

The **Children’s Global Adjustment Scale (CGAS)** [43] is an adaptation of the Global Assessment Scale (GAS) and will be used to assess psychosocial functioning**.** Research evaluation staff will rate the 100-point CGAS where scores above 70 indicate normal functioning, and scores less than 60 typically indicate the need for treatment.

#### Healthcare services, economic measures

Health Maintenance Organization (HMO) TAU healthcare services, including medications, will be obtained from the HMO **Electronic Health Record (EHR)** system through 12-month follow-up.

In order to capture any services youth may receive outside the HMO, we will administer the **Child and Adolescent Services Assessment (CASA)** [44]. The CASA is a youth- and parent-report instrument designed to assess the use of services by children ages 8 years to 18 years. The CASA includes 31 settings covering inpatient/outpatient visits, medications, and informal services provided by a variety of child-serving providers and sectors, and will be administered to collect data regarding non-HMO services. This instrument collects information on whether a service was ever used and more detailed information (length of stay/number of visits, focus of treatment) on services used in the recent past.

The **EQ-5D** [45, 46] is a 5-item measure that provides a single index value for health-related quality of life. Respondents rate their health state in five domains: mobility, self-care, usual activities, pain/discomfort, and anxiety/depression. It has good performance properties with anxiety disorders [47–49] and with children with a variety of health conditions [50]. The EQ-5D will be administered to parents and youth, to report on youth symptoms.

#### Other measures

**Demographic information** will be obtained at baseline: youth and parent age, birthdate, sex, race, ethnicity, religion, school status, health status, parent marital status, family composition (i.e., parent’s marital status), and socio-economic status (i.e., family income).

The **State Trait Anxiety Inventory (STAI)** [51] is a 40-item measure that assesses current and general feelings of anxiety, completed by parents about their own anxiety. There are two subscales, the State Anxiety Scale (STAI-S), and the Trait Anxiety Scale (STAI-T). The STAI-S will be administered to parents and asks how they feel “right now” or “at this moment.” The 20 items include measures of apprehension, tension, worry, and nervousness, as well as measures of calmness, security, and confidence. Each item is scored on a 1–4 scale and all items are scored such that higher values indicate greater anxiety. A total score ranging from 20 to 80 is created by summing all 20 items.

The **Peterson Pubertal Development Scale (PDS)** [52–54] is a self-administered, validated scale for pubertal development, including growth, changes in body hair, skin, and voice (for boys) or breast development (for girls). We will administer the abbreviated 5-item version. Each item is scored from 1 (developmental characteristic/sign not yet begun) to 4 (characteristic seems complete).

The **Insomnia Severity Index (ISI)** [55, 56] is a brief 7-item instrument that measures insomnia perception over the last month. It will be administered to the youth participants. The items comprise severity (difficulty falling asleep, staying asleep, and waking), satisfaction with current sleep pattern, interference of daily function, noticeability to others, and worry/distress caused by the sleep problems. Each item is scored on a 5-point Likert scale (range 0 to 4), with total score ranges from 0 to 28.

The **Participant Acceptability Questionnaire (PAQ)** is a youth- and parent-reported measure of the intervention acceptability and credibility, adapted from similar scales used by the Research Units on Pediatric Psychopharmacology. The PAQ asks about burden (e.g., boredom), beliefs and expectations about the intervention, and task comprehension.

The **Client Satisfaction Questionnaire (CSQ-8)** [57] is a measure of healthcare satisfaction with services received. Each item is scored from 1 to 4, for a total score ranging from 8 to 32, with higher scores indicating greater satisfaction with services. The CSQ will be given to youth and parents and will be a secondary outcome.

The **University of Rhode Island Change Assessment (URICA)** [58] is a 32-item readiness for change questionnaire. For this study, we used a shorter 12-item version, with statements describing how a person might feel when starting therapy or approaching problems in their lives. Youth participants indicate the extent to which they tend to agree or disagree with each statement. The URICA will be administered to youth participants.

**Instrumental Variables (IVs)** are measures that may permit an estimate of dose effect that is less biased than raw dose-outcome analyses [59, 60]. Candidate IVs need to be highly predictive of CBM dose but unrelated to unobservable characteristics that would confound estimates of the effect of CBM on outcomes. IVs will be collected at baseline and will include the characteristics of environment (e.g. privacy, location) where the youth plans to use the computer for the intervention, and the current use of electronic devices (e.g. hours of video games played per day).

### Interventions

Youth in all three arms will download one of two versions of the CBM program, depending on their study condition, and install it on their home computers. Neither youth, parent or assessment staff will know what CBM version is installed; all versions appear indistinguishable to users. Youth are asked to ideally complete three intervention sessions per week over a four-week period (a goal of 12 sessions total). Youth in all three study arms may receive non-research Treatment as Usual (TAU) for anxiety and other conditions, as delivered by the HMO or other healthcare providers. TAU may include CBT, other psychotherapies, and/or medications. We will collect data on receipt of TAU from the HMO’s EHR at the study conclusion, augmented with information about any services the youth may have received outside of the HMO during the follow-up assessments.

CBM procedures. The Low-Ratio CBM condition (Arm 1), and the two High-Ratio CBM conditions (Arms 2 and 3) share a common protocol for the delivery of the intervention. After eligibility is determined from the baseline assessment and the participant is randomized, they will be given a link and unique code to install the internet-based CBM program on their home computer. After registering with the program, the youth will complete a practice session over the phone with a study staff member. The same set of stimuli will be used for all three conditions, making the downloaded program appear identical to all users. Each youth will be instructed to complete three 15-min sessions per week for four weeks (12 sessions total). In each session, youth view 160 trials of a computerized probe detection task (simulated screenshots in Fig. 2). In each trial, two faces are briefly displayed one above the other, from a standardized set of 8 individuals. For all three CBM conditions, 80% of trials consist of neutral and negative (disgusted) face pairs, while the remaining 20% of trials consist of two neutral faces. Following a 500 ms presentation, the images disappear and a letter probe (either “E” or “F”) is displayed in the location where either the top or bottom face had just been. Youth are instructed to decide whether the letter was an “E” or an “F” with a left or right click of a mouse button. Youth do not receive feedback indicating the accuracy of their responses. In the 80% of High Ratio CBM trials (Arms 2, 3) where a neutral and disgusted face are present, the probe (E or F) always replaces the neutral face. In this manner, youth are trained to disengage their attention from threat. In the Low-Ratio condition (Arm 1), the probe replaces the neutral and disgusted faces with equal frequency (50–50%) in the trials containing both types of faces, and thus only minimal threat retraining occurs. The same library of stimuli is used for all training sessions. Images of faces will be used, rather than emotional words, because facial stimuli have been used in previous CBM studies with youths [24, 25, 61] and may control for differences in youths’ reading ability. Moreover, faces are the most common stimuli in CBM, across disorder type [62].

**Fig. 2 Fig2:**
[figure not shown]
Cognitive Bias Modification (CBM) program screenshots

Phone Coach Adherence Promotion (AP) (Arm 3 Only). AP procedures are intended to mimic the effects of the nonspecific, yet likely important, support and instruction provided by research staff when CBM has been traditionally delivered in laboratories. This includes technical assistance with use of the program, support/encouragement, motivational enhancement, and brainstorming solutions to barriers to regular sessions. We hypothesize that the addition of AP will lead to greater participant adherence to the program and therefore better clinical outcomes. In the first 4 weeks of each youth’s enrollment, phone coaches will make between one and four brief, 10–30 min AP telephone calls to youth enrolled in the High-Ratio CBM + AP condition (Arm 3). Coaches may also involve parents as appropriate. Call frequency will be determined by need, primarily based on the participant’s level of adherence to the CBM program. Participants who complete at least 80% of required sessions with a accuracy rate of 80% or higher will be considered adherent to the program. Youth who are most adherent to the protocol may receive only one or two AP calls from their coach, whereas youth with inconsistent or suboptimal use of the CBM program will receive more calls, up to a total of four. Phone coaches will receive automated adherence reports by logging into the server that stores the session data (e.g., number of trials, accuracy, reaction time). Phone coaches will use these reports to determine the need for AP calls, and the type of coaching they will provide (e.g., low accuracy rate and short reaction time might suggest that youth should slow down slightly to be more accurate). Calls do not need to be once weekly, but may be concentrated (e.g., twice weekly for the first few weeks) in order to facilitate participant engagement and maximize exposure to the CBM program. Coaches will record the date, duration, and content addressed in each call.

The phone coaches will provide the explicit rationale and instructions for the CBM intervention [29], as well as the “fear priming” instructions which encourage youth to activate anxiety fears prior to each CBM session to potentiate the effectiveness of CBM skills training [63]. The remaining content of phone coach calls will be individualized to the needs/issues of each participant, but will typically address: technical assistance (difficulty downloading CBM program, registering, creating a user account); encouragement and reinforcement for appropriate use; problem solving to overcome barriers and obstacles to use; using brief motivational enhancement techniques to encourage participants to use the program [30–32]; and/or coaching and advice to ensure high quality CBM sessions (e.g., conducting sessions at times/locations where participants will not be interrupted). If needed, phone coaches will also provide case-management and referrals for emergent clinical issues not addressed by CBM program (e.g., suicidality), although they will explicitly not themselves provide any psychosocial therapy for anxiety or any other issues.

**CBM Session review** questions will be asked of youth at 1-month follow-up. Questions ask about the number and length of sessions completed, which device was used, and interruptions during session completion.

### Treatment adherence and process data

CBM adherence data is also recorded automatically by the CBM program as part of its delivery across all arms. Number of sessions is calculated as the number of sessions completed from baseline to the 1-month follow-up. A session is defined as at least 160 completed trials. Quality of participation includes: missing data due to non-response, inaccurate responses (pressing random buttons), and probe response latencies outside of the task window (< 200 ms, > 3500 ms). As a check on the adequacy of our overall CBM implementation, we will benchmark the quality of participant performance against the CBM literature, for the total sample and by arm. Number of trainings and participation quality are also secondary outcomes, with the hypothesis that the Adherence Promotion arm (Arm 3) will show superior effects on anxiety due to an expected higher number of CBM sessions.

### Reliability ratings

#### Analysis plan

##### Data collection

At each telephone assessment research evaluation staff directly enter participant responses to interviews (e.g., the ADIS) or clinician rating forms (e.g., the PARS) into a RedCap data entry system. For later follow-up assessments, participants are given an opportunity to complete self-report measures directly on a RedCap survey page. Entered data values are limited to permitted ranges. This RedCap system is installed on the research Center data servers and receives daily backup along with all other research documents/databases.

##### Preliminary data evaluation

Prior to conducting data analyses, we will audit the data for completeness and quality, including missing data. We will evaluate distributions to ensure that they meet assumptions of planned analyses (see below), including the detection of outliers.

We will use a two-tailed α = .05 for the analyses of the primary outcomes. For the secondary outcomes, we will account for multiple testing by controlling the false discovery rate (10%) using the Benjamini–Hochberg procedure. All analyses will be carried out using the intent-to-treat principle by including all participants in analyses and their original arm assignments.

##### Statistical analysis

For each continuous outcome (anxiety symptoms [PARS, SCARED], depression [PHQ-9], psychopathology severity [CGI-S], psychosocial functioning [CGAS]) we will test whether there are differences between arms in the trajectories across time by fitting growth curve models in a nested two-level hierarchical linear model (HLM [64–66];).We will test the primary outcome (anxiety remission based on ADIS-C) and the CGI-I with a generalized form of HLM, using a logit link and the binomial distribution. For all HLM models, the first level of the model represents within-person variation and will include time as a predictor (3–5 timepoints, depending on the measure). The second model level represents between-person variation and includes dummy indicators for arm as the predictor variables. A significant coefficient for arm on the slope of time indicates (i.e., the cross-level interaction of arm by time) that there are different trajectories across time for each arm and will be followed with a graph to interpret the interaction(s). Assuming that the trajectories are nonlinear as is common in clinical trials (e.g., initial intervention effect upon completing the intervention and maintenance period), we will use fractional polynomials to estimate the most appropriate function for time [67, 68]. We will test our primary hypotheses using linear contrasts of the dummy vectors representing treatment arm to determine whether both High-Ratio CBM arms (2 and 3) have a different trajectory than the Low-Ratio arm, and whether High-Ratio CBM + AP (Arm 3) has a different trajectory than High-Ratio CBM Only (Arm 2). Differences at 1 month in acceptability (PAQ) and client satisfaction (CSQ-8) will be tested with a one-way ANOVA with treatment arm as the independent variable and the same a priori contrasts described above.

We will conduct the moderator analyses by adding the moderator and moderatorXarm product in the level-two HLM equation discussed above. A significant coefficient for the interaction term on the slope of time would indicate a moderator effect and will be followed up with graphs of the simple effects to determine the nature of the effect modification.

We will test whether attention bias mediates between treatment and the primary outcome (remission status), by regressing Wk 2 attention bias on attention bias at baseline and study arm indicators, and by regressing remission status (using logistic regression) at one month on attention bias at 2 weeks and study arm indicators. Using the product coefficients approach to mediation [69–71], we will use the resulting regression coefficients and standard errors (SEs) to estimate the indirect effect. Because SEs of the products of regression coefficients are not normal, we will use bias-corrected bootstrapping to estimate the SEs for the indirect effect [72].

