## Methods

### Design

This study is approved by the Kaiser Permanente Northwest (KPNW) Internal Review Board (IRB) in Portland, Oregon. This study is a randomized controlled trial (RCT), with participants blinded to the type of CBM they receive (low vs. high ratio) but not blinded regarding receipt of AP contacts. All evaluators are blinded to participant study condition.

Participants will be randomized via computer-programming to one of three arms in a 1:1:1 ratio, stratified by age at recruitment (< age 15 vs. > = age 15) and minority status (white non-Hispanic vs. all others). Assignment will be conducted with computer-generated random block sizes of 6 or 9, masked from study staff.

Arm 1 is a Low-Ratio version of the CBM intervention, nearly indistinguishable from the other CBM version but with a lower proportion of trials that shift attention to the neutral stimuli (details below). Arm 2 is a High-Ratio CBM program, with a higher proportion of trials shifting attention to the neutral stimuli. Arm 3 is the same High-Ratio CBM program but with a component consisting of adherence promoting (AP) telephone calls from a study phone coach, from 1 to 4 total as needed. All CBM programs are self-administered on participants’ home computers.

The primary clinical outcome will be diagnostic remission at 6-month follow-up from all anxiety diagnoses present at baseline, as confirmed by the Anxiety Disorders Interview Schedule (ADIS) (see below). The secondary clinical outcomes will be the PARS, SCARED, attention bias, depression (PHQ-9), psychopathology severity (CGI-S), and psychosocial functioning (CGAS). We will also determine whether there are differences in treatment acceptability (PAQ) and satisfaction (CSQ-8). Another secondary outcome will be cost-effectiveness of the CBM intervention, as measured in incremental cost per anxiety-free-day (AFD) and cost per quality adjusted life year (QALY). Additional analyses will test whether baseline CGI-S, PHQ-9 (depression), severity of cognitive bias (ADP), gender, socio-economic status, and race/ethnicity moderate the effect of the intervention on the primary outcome. Additionally, we will test whether attention bias mediates the effect of the intervention on the 6-month remission rate and anxiety outcomes (PARS and SCARED). Lastly, we will examine whether CBM process variables (i.e., number of trials [dose], acceptable error rates, reaction time) is associated with CBM outcomes.

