### Population and recruitment

Youth between the ages 12 to 17 years old will be enrolled from the KPNW healthcare organization, a large, non-profit health maintenance organization in the Pacific Northwest region of the USA. We aim to enroll a total of 498 participants in the study.

Potentially eligible youth will be identified by reviewing the healthcare organization electronic health record (EHR) for anxiety diagnoses (general anxiety disorder [GAD], anxiety disorder unspecified, or social phobia [SP], and/or separation anxiety). These are not qualifying criteria themselves, but a preliminary case-finding stage that identifies youth who are likely study eligible whom we will approach for recruitment. This initial EHR stage is meant to improve case-finding efficiency. Teen and parent participants will be recruited by mail, with a follow-up telephone call. Interested families will complete a brief, initial phone screening interview to determine if they meet preliminary inclusion and exclusion criteria. If preliminary eligibility criteria are met, parents and youth will give consent to participate in the full baseline assessment.

Inclusion criteria for this study include: age between 12 and 17 years old at enrollment; a research anxiety diagnosis confirmed by the ADIS at the baseline interview (see below); youth and parent able to complete assessments in English; youth access to a Windows home computer with Internet access. Exclusion criteria include: youth diagnosis of psychotic disorder; significantly impairing learning disorder or processing problem, such that completion of study procedures would be difficult; ADHD (except if symptoms are stable and controlled by medication for at least one month prior to enrollment); or youth primary complaint of condition other than anxiety. Comorbid diagnoses leading to study exclusion will be confirmed by reviewing the EHR.

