### Measures

#### Youth anxiety

The **Anxiety Disorders Interview Schedule for Children (ADIS-C)** [34, 35] is a semi-structured interview developed to identify the presence, severity, and level of interference of anxiety disorders in children aged 6–18 years old. It will be administered to youth and parents to yield Diagnostic and Statistical Manual of Mental Disorders (DSM) diagnoses of generalized anxiety disorder (GAD), social phobia (SP), and/or separation anxiety diagnoses needed to qualify for participation in the study. The trial primary outcome was also derived from this ADIS assessment: anxiety diagnosis remission at the 6-month follow-up. The ADIS will only be administered at the baseline, 6-month, and 12-month interviews. Before conducting ADIS interviews, staff must reach a criterion of 100% diagnostic correspondence with a senior staff on two consecutive interviews. All interviews will be digitally recorded; a random 10% of baseline assessments completed by each evaluation staff will be re-rated by a senior staff member.

The **Pediatric Anxiety Rating Scale (PARS)** [36] is a secondary outcome measure. This 50-item measure integrates youth and parent report of the severity of anxiety symptoms, as well as related functional impairment. Several versions of PARS scoring are available and used in the literature. To allow for comparison with other similar studies, we will calculate a total PARS score as the sum of items 2–7, with a total score ranging from 0 to 30 [37]. The PARS has high inter-rater reliability, fair internal consistency and test-retest reliability, convergent and divergent validity, and sensitivity to treatment effects [36, 38].

The **Screen for Child Anxiety Related Emotional Disorders (SCARED)** [39] is a 41-item measure of anxiety symptoms with youth- and parent-reported versions, with scores of > 25 indicating significant anxiety (total range 0 to 82). The SCARED has been validated in diverse clinical and community samples, with good internal consistency, and has detected clinical improvement in randomized clinical trials of treatment for youth anxiety [38]. We will examine the SCARED as a secondary outcome in this trial.

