We conducted power analyses for the primary outcome (via PASS software [77]) to generate the sample required to detect the hypothesized contrasts in a logistic regression model. For our main comparison of the two High-Ratio CBM conditions versus Low-Ratio CBM, with α = .05, we would have 80% power to detect a 20% greater remission (odds ratio = 2.90) in arms 2 + 3 compared to the Low-Ratio arm with 187 participants (n~ 63 per arm) at the 6-month follow-up**.** For the comparison of the two High-Ratio CBM conditions, at an alpha level of .05, we would have 80% power to detect a 16% greater remission (odds ratio = 1.94) in the CBM + AP arm compared to the CBM only arm with 148 participants per arm (*N* = 444 total) at the 6-month follow-up. We based our target sample on the larger N needed to adequately test this latter hypothesis (Arm 2 vs. Arm 3). To compensate for the loss in precision from imputing data for those lost to follow-up, we inflated the target sample size based on an attrition rate of ~ 10% (*N* = 498, or *n* = 166 per arm). This is a conservative adjustment, as the SEs from imputed data results will be less than the SEs from a complete case analysis.

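### The primary outcome is remission at 6 months, but the stated test is an arm-by-time slope over months 0, 6 and 12: it does not isolate the 6-month difference, and the 80% power was computed for another test

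*Protocol article*

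**What the plan says.** **Outcome.** The Design section states: "The primary clinical outcome will be diagnostic remission at 6-month follow-up from all anxiety diagnoses present at baseline". The Abstract and the Youth anxiety section give the same time point.

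**Sample size.** The Power analyses section used software "to generate the sample required to detect the hypothesized contrasts in a logistic regression model", with remission at the 6-month follow-up. For Arm 3 v Arm 2 it gives 80% power for 16 points (odds ratio 1.94) with 148 per arm, and this comparison sets the target of 498.

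**Test.** The Statistical analysis section says: "We will test the primary outcome (anxiety remission based on ADIS-C) and the CGI-I with a generalized form of HLM, using a logit link". For every such model, level one "will include time as a predictor (3–5 timepoints, depending on the measure"; level two holds the arm indicators. The decisive result is described as follows: "A significant coefficient for arm on the slope of time indicates" that trajectories differ by arm. The primary hypotheses are contrasts of trajectories, for example "whether High-Ratio CBM + AP (Arm 3) has a different trajectory than High-Ratio CBM Only (Arm 2". Fractional polynomials choose the time function.

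**Data available.** "The ADIS will only be administered at the baseline, 6-month, and 12-month interviews". Entry requires "a research anxiety diagnosis confirmed by the ADIS at the baseline interview".

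**The concern.** The outcome and its power belong to one question: do the arms differ in remission at month 6? The test belongs to another: do the arms differ in slope over the year? No sentence ties the second to the first.

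The time points make this worse. Among the repeatedly measured outcomes assigned to these models, Table 1 gives five occasions for PARS, SCARED, PHQ-9 and CGAS, and four for CGI-I. Only the ADIS can supply the lower end of the stated range of three to five, and it does so only if baseline counts. Remission from the diagnoses present at baseline is zero at baseline for every participant, so the logit there is minus infinity. The fitted starting level is then set by the time function. The better that function fits month 0, the closer the model comes to separation.

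At stake is whether a significant primary result means a 6-month difference, and whether a real 6-month difference is tested with the stated power. Both primary contrasts inherit the problem. So do the moderator analyses of the primary outcome, which use the same slope criterion.

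**Working it through.** **1. The plan's own figure.** Solve p and p + 0.16 for an odds ratio of 1.94. There are two solutions:
- 34.1% v 50.1%: (0.501/0.499)/(0.341/0.659) = 1.94
- 49.9% v 65.9%: (0.659/0.341)/(0.499/0.501) = 1.94

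The two-proportion formula, two-sided 0.05 and 80% power, with mean rate 0.421, gives

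n = [1.960·√(2·0.421·0.579) + 0.842·√(0.341·0.659 + 0.501·0.499)]² / 0.16² = (1.3685 + 0.5799)² / 0.0256 ≈ 148 per arm.

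The second solution is the mirror image and gives the same n. So 148 reproduces as a direct 6-month comparison.

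**2. What the slope measures.** Write logit(p_t) = b0 + b1·arm + (b2 + b3·arm)·f(t) + u, with b3 tested. The article does not say whether b1 is in the model.
- *Arm on intercept and slope.* The arm effect at month t is b1 + b3·f(t). An equal effect at months 6 and 12 is b1 = log OR and b3 = 0, so the follow-up visits carry no signal for b3. What signal there is comes from the all-zero baseline. In simulation without baseline, a constant odds ratio of 1.94 gave a significant slope in only 4–5% of trials.
- *Arm on slope only.* The effect is b3·f(t). With linear time, the log odds ratio at month 12 is forced to be 12/6 = 2 times that at month 6. With log(t+1) the factor is ln 13/ln 7 = 2.565/1.946 = 1.32. Month 12 therefore helps decide b3.

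**3. Power of the slope test.** From the article: 148 per arm, two-sided 0.05, remission zero at month 0, and the rates in step 1. My assumptions: random-intercept logit fitted by maximum likelihood, 6-/12-month correlation 0.6, time linear or log(t+1), and the 12-month rates shown. The model is fitted to expected counts with and without b3. With λ as the likelihood-ratio statistic, power = Φ(√λ − 1.96) + Φ(−√λ − 1.96). Example (34% v 50% sustained, linear time, arm on both): λ = 1.467, √λ = 1.211, power = 0.227 + 0.001 = 0.23.

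| True remission, Arm 2 v Arm 3 | Arm on intercept and slope (linear / log) | Arm on slope only (linear / log) |
|---|---|---|
| 34% v 50% at months 6 and 12 | 23% / 17% | 89% / 90% |
| 50% v 66% at months 6 and 12 | 41% / 27% | 94% / 92% |
| 34% v 50% at 6; 50% v 50% at 12 | – | 7% / 15% |
| 34% v 34% at 6; 34% v 50% at 12 | 68% / 56% | 80% / 65% |

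In the last row there is no 6-month difference, so every positive result is a wrong answer to the primary question.

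**4. Simulation check.** A separate simulation used 42% remission in Arm 2 at month 6 and 148 per arm.
- *Odds ratio 1.94 at both visits:* arm on both gave 17–24% (linear) and 1–9% (log); slope only gave 94–98%. The direct 6-month test gave 81–87%.
- *Effect gone by month 12:* slope only gave 16–37%, the upper end with inverse time.
- *Effect only at month 12:* positive in 45–73% (arm on both) and 46–78% (slope only). The 6-month test was positive in 6.5%.
- *No effect at either visit:* arm on both rejected in 0–0.5%, far below 5%, so the chi-square approximation in step 3 is rough for that version.

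**The case against.** The strongest reply concerns size. The article does not say which level-one coefficients carry the arm indicators. With remission zero for all at baseline, a common intercept is a natural choice, and then a sustained effect is detected with 89–94% power, above the stated 80%. If the odds ratio grew from 1.94 at month 6 to 3.0 at month 12, even the version with arm on both reached 91% with linear time in simulation (58–61% with log time). The correlation, 12-month rates and random-effect structure are my assumptions. This stands: a reader might infer that the trial would usually miss a sustained 16-point gain, or that power is simply 5–25%, and the document supports neither. Nor do 16 points and an odds ratio of 1.94 fix one pair of rates; two pairs fit, and the second gives higher slope-test power.

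A reader might also infer that the result is read from a graph. It is not: a coefficient and linear contrasts are tested, and the graph only helps to interpret an interaction.

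Finally, an unseen analysis plan may centre time at month 6 or add a 6-month estimate. That is possible. But the article positively states a slope criterion and trajectory contrasts for the primary hypotheses. This is a stated rule that conflicts with the outcome, not a detail left out.

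**Conclusion.** The point holds as a mismatch between the primary outcome and its test. The article defines and powers remission at month 6, then tests a slope that includes an all-zero baseline and is shaped by month 12 and by a data-chosen time function. The stated 80% power does not belong to that test.

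How far true power departs from 80% cannot be read from the document. Under the assumptions shown, it runs from well below (about 17–41%, arm on both, sustained effect) to above (about 89–94%, slope only, sustained effect). It falls to about 7–15% for slope only if Arm 2 catches up from 34% to 50% by month 12. The conclusion that does not turn on the intercept choice is about interpretation: with a difference only at month 12, the primary test is positive in about 56–80% of trials under either version.

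This should be corrected, because it decides whether the primary result answers the primary question.

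**What to change.** Define the primary test as the two planned arm contrasts (Arms 2 and 3 v Arm 1; Arm 3 v Arm 2) in ADIS remission at 6 months.

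- **Preferred model:** a likelihood-based logit model of the post-baseline visits only (T3 and T4), with visit categorical and arm-by-visit terms, and the T3 contrast named as primary. This keeps the direct maximum likelihood handling in the Missing data section.
- **Alternative:** logistic regression at T3, the model on which the sample size rests. It drops participants without a 6-month ADIS unless they are imputed, which sits badly with the stated intention to include all participants.
- Remove baseline remission and the fractional-polynomial slope test from this outcome.
- Report 12-month remission as secondary.
- Test moderators of the primary outcome as moderator-by-arm at T3.
- Report the odds ratio and the risk difference at 6 months.

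The cost is wording in the analysis section or the analysis plan; no new data or participants are needed. The 12-month ADIS no longer drives the primary test.
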